### Nested qualitative study

Data regarding the implementation of JoL will be collected through qualitative interviews at baseline and endline, and through a process evaluation. Interviewers will conduct key informant interviews (KIIs) with implementing staff, community partners, and participants at baseline and endline. Sample sizes for qualitative data collection will be oriented with the aim of reaching saturation [42]. Data will be analyzed using Dedoose [43]. The process evaluation will draw on routine monitoring tools, including activity sheets, attendance and observation checklists.

### Data management

Participants names will not appear on any collected data; they will each be assigned a unique study ID. Quantitative survey data collected on tablets will be uploaded to the secure server directly by the research coordinator, from which it will be downloaded to Washington University in St. Louis’ secure server and entered into STATA. Qualitative data will be similarly downloaded to a secure server and entered into Dedoose. All non-digital data (e.g. consent forms, activity sheets, and attendance and observation checklists) will be stored securely at the implementation site office, and all data and analysis files will be securely password protected and encrypted. For all quantitative survey data, range and consistently checks will be performed within a few days of data collection. De-identified qualitative data will be translated and transcribed verbatim and entered in Dedoose where they will be coded and analyzed by the research team.

### Adverse events

There is minimal risk to participant safety or wellbeing from participation in this study due to the non-pharmacological and non-clinical nature of this intervention. The occurrence of adverse events (AEs) will be monitored through a standard Adverse Event Reporting Procedure. All AEs reported by enumerators will be recorded by the research team, discussed with the research coordinator and referred to appropriate support services within 24 h of notification.

### Ethics

All study procedures were approved by the Washington University in St. Louis Institutional Review Board (IRB) and by an in-country IRB (TASO Uganda). Eligible participants will be systematically screened by interviewers to determine that they meet the inclusion criteria and are competent to be interviewed. Everyone participating in the intervention will be invited to participate in the baseline and endline surveys to track participant changes. Data collection staff will be trained and available to respond to any questions on the consenting process. Consent will be explained to participants verbally and in a written format, participants will sign written consent for participation.

### Effectiveness outcomes

All questionnaire data will be gathered using Android tablets. Measures will be administered in Juba Arabic, Dinka, Nuer, and Acholi (languages covering the majority of the population) by trained and supervised enumerators. In order to capture key demographic information, the survey contains questions related to age, gender, marital status, years of education, current sources of income, and caregiving status. Survey modules cover functioning, social support, experiences of intimate partner violence, mental distress, child protection behaviors, and parenting styles. See Table 1 for a detailed overview of measures.

**Table 1 Tab1:** Outcome Measures

Measure	Tool	Description
Mental distress	Kessler-6	The Kessler-6 asks participants how frequently they have experienced certain symptoms in the past thirty days and presents a consistent range of responses ranging from “1 - All of the time” to “5 - None of the time” [44]. The scale shows consistency across multiple socio-demographic variables and has been previously documented among refugees in Uganda [45].
Functioning	World Health Organization Disability Assessment Schedule	WHODAS assesses functioning through six domains of cognition, mobility, self-care, interpersonal skills, life activities, and community participation. The WHODAS has been used in international settings including Uganda Bachani et al. [46].
Social Support	Medical Outcomes Study (MOS)	The MOS measures social support across five dimensions, including: 1) emotional, 2) informational, 3) tangible, 4) positive social interactions, and 5) affection. It has been used to assess social support among individuals affected by HIV in Uganda [47–49].
Parenting behaviors	Parenting Acceptance and Rejection Questionnaire	For the purposes of this study, the subscales of warmth/affection, hostility/aggression, indifference/neglect, and undifferentiated rejection will be used. The PARQ has been used in similar settings to assess parenting behaviors [50].
Attitudes towards child protection	Child Protection Index	Items related to perceptions on the treatment of children, child rearing, and educating children are included in this study. Developed in collaboration with the UNHCR, AVSI, and the CPC Learning Network, the Child Protection Index, assesses child protection outcomes in displacement settings Meyer et al. [51], and has been used previously in Uganda Meyer et al., [6, 52, 53].
Intimate partner violence	WHO multi-country Violence Against Women (VAW) study	These items estimate the prevalence of physical, sexual, and emotional violence against women. The World Health Organization (WHO) Multi-country study on Women’s Health and Domestic Violence included the collection of data from over 24,000 women in 10 countries.

### Implementation measures

Frameworks such as FRAME (Framework for Reporting Adaptations and Modifications-Expanded) provides a structure to analyze program adaptations pre-, during, and post-implementation [54]. FRAME includes [1] when and how adaptations were made, [2] whether the adaptations were unplanned/reactive or planned/proactive, [3] who determined the adaptation, [4] what was adapted, [5] at what level of delivery the adaptation was made, [6] the type of adaptation, [7] the extent to which the adaptation is consistent with fidelity, [8] the reasons for the adaptation. Adaptations, including the successful tailoring of evidence-based practices for the target population, may improve participant involvement and overall clinical outcomes.

Additionally, components of the CFIR (Consolidated Framework for Implementation Research) [55] will be integrated into qualitative semi-structured KIIs at baseline and endline with implementation staff, community organization partners, and community members in order to address implementation components, including acceptability, feasibility, and others outlined in Table 2. Findings from KIIs will be used to inform program adaptations and record implementation indicators. Additional indicators will be tracked using monitoring and evaluation (M&E) approaches such as tracking attendance, and monitoring fidelity to program components using observation checklists.

**Table 2 Tab2:** Implementation science framework for JoL assessment

Construct	Short Description	Collection Method
**Intervention characteristics**		
Acceptability	Define if the program feels acceptable to community stakeholders	KII
**Outer setting**		
Needs & Resources	Community needs and available supportive resources.	KII
Cosmopolitanism	Organizational network and connections with other organizations.	KII
**Inner setting**		
Culture	Organizational norms, values, and customs.	KII
Feasibility	Defining barriers and facilitators in order to address potential adaptions to the implementation strategy and manualized tools.	KII
**Characteristics of individuals**		
Self-efficacy	Belief in one’s own capabilities to execute the implementation plan.	KII
Attendance	Track attendance at weekly sessions and reasons for not attending	M&E
Execution	Delivering the program according to plan.	KII
**JoL Components**		
Adaptations	Tailoring the intervention to population and context specific needs.	KII
Group composition	The composition of groups, including demographics of participants.	
Space procurement	The proposed location of the JoL groups.	KII
Scheduling	The best time of day and/or day of the week to meet	KII
Attrition	Barriers and facilitators to retention	KII
Fidelity	Track fidelity to program components using observation checklists	M&E

### Data analysis

#### Quantitative analysis

The analytic plan is designed to assess effectiveness of the JoL intervention on MHPSS and caregiving behaviors. The level of significance for all analyses will be set at 5%. We will initially assess the sample in terms of baseline characteristics. Other preliminary data analyses will include studies of patterns of missing data, dropout rates, distributional properties of dependent and other measures, and correlations among outcomes. We will determine if effectiveness differs meaningfully in the intervention group compared to the control group. As the primary intervention is community based, an individual’s specific exposure to intervention activities (e.g. intervention dose received) will not be explored, but rather all individuals within the intervention group will be categorized as intervention respondents and all individuals within the control group will be categorized as control respondents. We will also assess the effect of potential mediators in the causal pathway between treatment and outcome. To explore if efficacy differs by baseline characteristics (moderation), we will model the outcomes with the relevant baseline characteristics and their interaction as predictors. Factor-stratified models (e.g. by gender) may be explored if interaction terms are found to be statistically significant. Our modeling approach to assess changes in outcomes over time will use generalized mixed models for longitudinal data. This class of models does not assume that subjects are measured at all time-points, and therefore can include subjects with two measurement time-points. In these analyses, we will examine changes across time in order to assess – and isolate from programmatic efficacy - the effect of time. Based on intervention attendance records, both intention-to-treat and per-protocol analyses will be explored. We will also conduct sensitivity analyses to investigate the robustness of results across different models for missing data, following this detailed approach. Additional analyses will also be explored, such as the need for models that use inverse probability weighting to account for potentially high levels of incomplete intervention participation within the intervention community.

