**Methods:**

A waitlist-control quasi-experimental design is being implemented in the Kiryandongo refugee settlement (intervention *n* = 600, control *n* = 600). Caregiver mental distress, measured using the Kessler-6, was selected as the primary outcome. Secondary outcomes include (a) functioning measured by the World Health Organization Disability Assessment Schedule, (b) social support measured by the Medical Outcomes Study Social Support Survey, and (c) caregiving behaviors according to the Parental Acceptance and Rejection Questionnaire and the Child Protection Index. The study aims to examine the implementation of the JoL intervention through qualitative assessments of intervention feasibility, adaptations, and reach.

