### Study design

The proposed study will evaluate the effectiveness and implementation of the JoL intervention using a quasi-experimental waitlist control design. In order to reduce contamination, the treatment group will be conducted in one Ranch (a demarcated segment of the settlement) of Kiryandongo, while the wait-list control group will be in a Ranch that is geographically separate. Participants in the intervention group will receive the program weekly for 12 weeks. The waitlist control group will be invited to participate in the intervention shortly after the endline assessment in the intervention group has been completed (see Fig. 1). Effectiveness indicators will be assessed at baseline and endline.

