### Recruitment and population characteristics

Participant recruitment will be conducted in collaboration with the staff of the implementing organization and their community partners. Inclusion criteria for participation in JoL is any person (men and women) ages 18 and over who lives with a child under 18 years old or has caregiving responsibilities for someone under the age of 18. Participants can be refugees or Ugandan nationals living in the study location, they do not need to meet any criteria for adverse mental health, including stress or mild mental illness. Additionally, individuals who have experienced an adverse mental health event are not excluded from the study. Exclusion criteria for the intervention includes anyone aged 17 and under and anyone who is not able to consent to participate.

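### With one non-randomised Ranch per arm, the stated analysis does not adjust the between-Ranch comparison for case mix, so the primary estimate is open to confounding of change

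*Protocol article*

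**What the plan says.** The Study design section describes an evaluation "using a quasi-experimental waitlist control design". On the intervention arm it states that "the treatment group will be conducted in one Ranch (a demarcated segment of the settlement) of Kiryandongo", and on the control arm that "the wait-list control group will be in a Ranch that is geographically separate". The reason given for separating the Ranches is contamination, and the Discussion repeats this as spillover. Neither place discusses whether the two populations are comparable.

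In the Quantitative analysis section, baseline characteristics appear twice. The first is descriptive: "We will initially assess the sample in terms of baseline characteristics". The second is moderation, where they enter with an interaction to see whether efficacy differs between subgroups. The outcome model is a generalised mixed model for longitudinal data on the baseline and endline measurements, intended to separate the effect of time from that of the programme. Weighting is named once, among additional analyses to be explored: "models that use inverse probability weighting to account for potentially high levels of incomplete intervention participation within the intervention community".

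On who is enrolled, the recruitment section says "Participants can be refugees or Ugandan nationals living in the study location". On what is recorded, the Effectiveness outcomes section says "the survey contains questions related to age, gender, marital status, years of education, current sources of income, and caregiving status". Refugee or national status is not in that list.

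**The concern.** In a study that allocates by place of residence, the first analytic question is how to deal with two groups that may contain different people. The article is fairly detailed on other matters: mediators, moderators, stratified models, per-protocol analysis, missing-data sensitivity and weighting for participation. It names no method for this one.

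If caregivers in the two Ranches differ in income, education, caregiving load or refugee status, and if distress would have moved differently over 12 weeks in those subgroups without any programme, the group-by-time contrast credits that difference to JoL or charges it against JoL. The Dissemination section makes scale-up conditional on JoL being shown effective, so an error in either direction matters. The study's objective concerns caregivers in a refugee camp. An unlisted refugee status therefore also bears on whether the result can be reported for refugees separately.

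**Working it through.** **The plan's own figure.** The sample size section gives 1200 × 0.80 = 960 retained, or 480 per arm; this reproduces. Its 80% power for an 11% effect cannot be reproduced without a control proportion, which is not given. It has no bearing on confounding and is not used here.

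**What the stated model removes.** Let G = 1 for the intervention Ranch, t = 0 at baseline and 1 at endline, and X a baseline characteristic. Suppose the score is

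Y = a + bG + ct + dGt + eX + gXt + error.

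Here b is a stable level difference between Ranches, d is the programme effect, e is the effect of X on level, and g is its effect on change. For one person, endline minus baseline is

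change = c + dG + gX.

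Both b and eX have cancelled, so level differences are dealt with. Averaging within Ranch and subtracting gives

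expected contrast = d + g × (mean X in intervention Ranch − mean X in control Ranch).

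The second term is the bias. It is zero only if X is balanced between Ranches or has no effect on change. The article provides for neither.

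**What would and would not help.**
- X as a main effect only: eX has already cancelled, so the contrast barely moves.
- X-by-time term: estimates g and removes the second term.
- Weighting on propensity for Ranch: makes the two means of X equal and removes the second term.
- A Ranch-level event or service change of size u adds uGt. The contrast becomes d + u, and with one Ranch per arm nothing in the data separates the two.

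**Size, under assumed inputs.** The article gives neither the imbalance between Ranches nor any subgroup trend, so everything below is an assumption apart from 480 per arm and the 5% level (taken as two-sided). Bias = imbalance × difference in 12-week trend:

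- 10 points × 0.1 SD = 0.01 SD
- 20 points × 0.3 SD = 0.06 SD
- 30 points × 0.5 SD = 0.15 SD

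The comparator must be the standard error of a difference in change, which depends on the baseline–endline correlation ρ (not given). Ignoring clustering, SE = √(2(1 − ρ)) × √(2/480), with √(2/480) = 0.0645 SD.

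| ρ (assumed) | SE (SD) | False-positive risk at bias 0.01 | at 0.06 | at 0.15 |
|---|---|---|---|---|
| 0.3 | 0.0764 | 5% | 12% | 50% |
| 0.5 | 0.0645 | 5% | 15% | 64% |
| 0.7 | 0.0500 | 5% | 22% | 85% |

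Each risk is P(Z > 1.96 − bias/SE) + P(Z < −1.96 − bias/SE) with no true effect. The range runs from negligible to serious, and the documents do not say where this study falls.

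**The case against.** The strongest reply is that this is a condensed article. A covariate set for adjustment commonly sits in the analysis plan, and the article does not forbid adjustment: the weighting sentence is offered as an example of further analyses, not as a closed list. In addition, the outcome is measured before and after in both arms, which is a real safeguard.

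The second part stands in full. A reader might infer that the primary contrast is confounded. The documents do not support that: stable differences in level cancel, and no figure shows that the Ranches differ or would have diverged. The 17% refugee share in the Setting section describes a population of about 313,800; it gives no refugee share for either Ranch or for the sample, so it is not evidence of imbalance.

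The first part stands only in part. The article does specify how baseline characteristics and weighting will be used, and it points both at other questions. In a non-randomised comparison, adjustment for case mix belongs in the primary analysis and is more than a detail.

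A reader might also infer that refugee status goes unrecorded. The list of demographic items is not said to be complete, so the supportable statement is that status is not listed. Lastly, weighting would not make the comparison as good as randomised, because Ranch-level effects stay aliased with treatment whatever individual covariates are used.

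**Conclusion.** The point holds in a limited form. Beyond the baseline-to-endline comparison, the article states no adjustment of the between-Ranch contrast, and the weighting it names serves a different purpose. The primary estimate is open to confounding of change through case mix. It is unbiased only if the two Ranches would have changed in parallel without JoL. The article does not state that assumption, and two measurement times cannot test it.

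No size can be fixed from the documents. The 0.01 to 0.15 SD range is illustrative, for a single binary covariate with assumed imbalance and trend difference and with clustering ignored. The conclusion does not depend on it; it rests on the one-Ranch-per-arm design and on the stated roles of covariates and weights.

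**What to change.** 1. Make the primary estimate one that is adjusted for measured case mix, using items already planned: age, gender, marital status, education, income, caregiving status, and baseline functioning and social support.
2. Do this either with covariate-by-time terms in the mixed model or with propensity weights for Ranch, and name the choice in advance. Main effects alone are not enough. If weights are used, state the target population, since overlap weights in particular change it.
3. If baseline Kessler-6 is to be used for adjustment, use an endline model conditional on it, and do not also treat it as an outcome in the same model.
4. Report balance between Ranches before and after adjustment, and show the unadjusted estimate alongside.
5. If refugee or national status is collected, say so and include it. If not, add the item; it can be asked at endline if baseline has passed.
6. State that the result assumes parallel change between Ranches, and that with one Ranch per arm Ranch-level events cannot be separated from the programme.

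The cost is plan wording, at most one survey item, some loss of precision and slightly more analysis. The sixth step limits what can be claimed; no analysis of this design removes that limit.

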#### Qualitative analysis

On-going qualitative analyses will be conducted over the course of the study to explore new and unexpected themes that arise; we will shift to new questions when saturation is reached. Using Dedoose, multiple study staff members will independently code 10% of the transcripts and compare the application of the coding scheme to assess its reliability and robustness; we will resolve disagreements through discussion.

Systematic analysis of the various types of data collected will be conducted using a grounded theory approach. Grounded theory analysis requires that data be analyzed continuously throughout the duration of data collection, so that theories generated from the data can be used to direct and inform subsequent research efforts. In grounded theory, the researcher summarizes initial observations into conceptual categories and then tests the coherence of the categories in the research setting with additional observations so that theory evolves but is grounded in data from subsequent observations. An initial codebook and coding scheme will be developed and expanded as the data are analyzed.

We will use the content analysis techniques, *repetitions* and *cutting and sorting*, to identify themes in the data. These content analyses techniques involve identifying the recurrence of words/phrases (*repetitions*), and recognizing patterns in quotes and expressions that are salient and that can be distinguished from other patterns in the data (*cutting*), then organizing them together (*sorting*).

#### Dissemination

The results of this project will be disseminated internally among implementation staf of TPO and REPSSI about the use and implementation of JoL. Results will be shared in verbal and written formats to ensure accessibility. Additionally, presentations about outcomes will be organized for UNHCR agency meetings both in settlement locations and among agencies in Kampala. Other forums for dissemination will include annual research meetings and forums virtually and in-person. If JoL is proven to be effective, the adapted manual will be shared with program developers, implementation staff, and key partners in order to facilitate scale up of implementation. REPSSI will also disseminate the adapted manual across countries of operation. Furthermore, results will be published in English in peer-reviewed journals for regional and global audiences.

